# Efficacy and cost-effectiveness of a community-based model of care for older patients with complex needs: a study protocol for a multicentre randomised controlled trial using a stepped wedge cluster design

**DOI:** 10.1186/s13063-018-3038-0

**Published:** 2018-12-04

**Keywords:** Model of care, Comprehensive geriatric assessment, Integrated care, Effectiveness, Cost utility analysis, OPEN ARCH, Complex care needs, Elderly, Quality of life

## Abstract

**Background:**

Community-dwelling older persons with complex care needs may deteriorate rapidly and require hospitalisation if they receive inadequate support for their conditions in the community.

**Intervention:**

A comprehensive, multidimensional geriatric assessment with care coordination was performed in a community setting—Older Persons ENablement And Rehabilitation for Complex Health conditions (OPEN ARCH).

**Objectives:**

This study will assess the acceptability and determine the impact of the OPEN ARCH intervention on the health and quality of life outcomes, health and social services utilisation of older people with multiple chronic conditions and emerging complex care needs. An economic evaluation will determine whether OPEN ARCH is cost-effective when compared to the standard care.

**Methods/design:**

This multicentre randomised controlled trial uses a stepped wedge cluster design with repeated cross-sectional samples. General practitioners (GPs; *n* ≥ 10) will be randomised as ‘clusters’ at baseline using simple randomisation. Each GP cluster will recruit 10–12 participants. Data will be collected on each participant at 3-month intervals (− 3, 0, 3, 6 and 9 months). The primary outcome is health and social service utilisation as measured by Emergency Department presentations, hospital admissions, in-patient bed days, allied health and community support services. Secondary outcomes include functional status, quality of life and participants’ satisfaction. Cost-effectiveness of the intervention will be assessed as the change to cost outcomes, including the cost of implementing the intervention and subsequent use of services, and the change to health benefits represented by quality adjusted life years.

**Discussion:**

The results will have direct implications for the design and wider implementation of this new model of care for community-dwelling older persons with complex care needs. Additionally, it will contribute to the evidence base on acceptability, efficacy and cost-effectiveness of the intervention for this high-risk group of older people.

**Trial registration:**

Australian New Zealand Clinical Trials Registry, ACTRN12617000198325p. Registered on 6 February 2017.

**Electronic supplementary material:**

The online version of this article (10.1186/s13063-018-3038-0) contains supplementary material, which is available to authorized users.

## Background

The Australian healthcare system experiences significant demand in health service utilisation due to an aging population coupled with more complex health conditions [1]. Complex health conditions are the leading cause of illness, disability and death in Australia, accounting for 90% of all deaths in 2011 [1]. Hospitalisation for many complex conditions is preventable, yet they remain the most common hospital admission category [1].

Community-dwelling older patients with complex health needs may deteriorate rapidly and face hospitalisation if their conditions are poorly managed or poorly coordinated in the community. Once hospitalised, these often frail individuals may face excessively long hospital stays, which in turn increase their risk of hospital-acquired infections, delirium, falls and cognitive decline [2]. They become more dependent and may require permanent placement in a residential aged care facility, rather than returning home as a self-caring individual. It is not unusual for such patients to be hospitalised without great acute need.

Strong evidence suggests that older people will have better health outcomes if appropriate preventative care is provided in the community and early in the trajectory of the person’s illness [2]. In 2009 the National Health and Hospital Reform Commission (the Commission) recommended major changes to the health service delivery for patients with complex needs [3]. Of central interest are older people with interrelated medical, functional and psychosocial issues, increased risk of functional deterioration and unplanned institutional care. The Commission reinforced the task to expand specialist services in the community to address the needs of older people [3]. Several such models of care have been developed. In comprehensive geriatric assessment, such as the geriatric evaluation and management (GEM) model of care, an interdisciplinary team of healthcare professionals assesses an older person’s medical, functional, psychosocial, nutritional and environmental needs [4]. This interdisciplinary team creates a comprehensive plan of care that is communicated to the person’s physician. The model demonstrats a multidisciplinary, coordinated solution designed to facilitate care transition and improve health outcomes for older people with multidimensional health needs [4].

Published programmes utilising the GEM in Australia have shown promising results, including the Victorian Hospital Admission Risk Program, which reported 35% fewer Emergency Department (ED) attendances, 52% fewer admissions and 41% fewer days in hospital [5]. Similarly, the Reengineered Hospital Discharge Program [6], Better Outcomes for Older Adults Through Safe Transitions and State Action on Avoidable Re-hospitalisations programmes have shown improvements in reducing hospital readmissions and hospital utilisation such as length of stay [7]. The Geri-FITT model of care which involves a ‘floating interdisciplinary geriatric team’ to provide continuity of care through developing and facilitating transitional care plans and educating patients and care providers about geriatric care principles has demonstrated improved quality care transitions and greater patient satisfaction [8].The most similar study to the one proposed here was the ‘Patients First Model of Care’, which targeted people over 55 years old who frequently presented to the ED or were at risk of presenting to the ED. This study involved a comprehensive needs assessment by a community-based care facilitator, with care coordination and facilitation of access to a suite of services including allied health therapies where required. Findings from this community coordinated study reported a 27.9% reduction in hospital admissions and a 19.2% reduction in bed days without increasing overall costs to the health system [9].

Recent research on care transitions of older people across acute, sub-acute and primary care identified underutilisation of the GEM model in a community setting in north-eastern Australia [4]. In this region, an integrated model of comprehensive geriatric assessment, care coordination and rehabilitation is currently only available for hospital in-patients, with no preventative services available to prolong independent community living. Furthermore, sub-acute services for community-dwelling older persons are found to be fragmented; the access to health pathways is unclear, potentially leading to a perverse incentive for hospital admissions to access in-patient geriatric services.

This trial aims to address the gap by delivering and evaluating a comprehensive, multidimensional geriatric assessment with care coordination in a community setting. The Older Persons ENablement And Rehabilitation for Complex Health conditions (OPEN ARCH) model of care evolved from an initial study that explored patient well-being post hospitalisation [10]. That completed study examined patients’ transition back to primary healthcare and their access to allied health and social support services within the community [10]. This current OPEN ARCH intervention builds on previous research [4, 10] and extends the service to preventative service delivered in a community setting; it creates a direct path from a general practitioner (GP) to a community-based geriatrician-led Healthy Ageing Clinic for comprehensive interdisciplinary assessment and care planning. The OPEN ARCH intervention will facilitate timely access to primary healthcare, including allied health services and social supports within the community. It is envisaged that the OPEN ARCH intervention will delay health decline by increasing individual capacity, when supported by a team of community healthcare professionals, who monitor and manage the community-dwelling complex older patients within the community. Such coordinated care support is expected to reduce the likelihood of the aforementioned cascade of events that leads to hospitalisation, and eventual loss of independence following hospital discharge.

## Objectives

The objective of the study is to assess the acceptability of the OPEN ARCH intervention and its impact on the health and quality of life outcomes, health and social services utilisation of older people with multiple chronic conditions and emerging complex care needs. An economic evaluation will determine whether OPEN ARCH is cost-effective when compared to the standard care. In particular, this study will address the following research questions:Does the OPEN ARCH intervention result in reduced hospital care demand as measured by Emergency Department (ED) presentations, hospital admissions and in-patient bed days?Does the OPEN ARCH intervention result in reduced functional decline and dependency, and enable patients to live in the community for longer?Does the OPEN ARCH intervention result in an improved quality of life for participants?Is the OPEN ARCH intervention considered by participants to be an acceptable model of care?Is the OPEN ARCH intervention a cost-effective means to achieving better health and quality of life outcomes for at-risk older persons when compared to standard care?

## Methods

The items in this study protocol comply with the Standard Protocol Items: Recommendations for Interventional Trials (SPIRIT) checklist (see the SPIRIT Checklist and figure in Additional file 1 and Fig. 1) [11, 12]. Adherence to SPIRIT allows transparency and completeness of the trial protocol for the benefit of investigators, trial participants, research ethics committees and other key stakeholders [11].

**Fig. 1 Fig1:**
[figure not shown]
Standard Protocol Items: Recommendations for Interventional Trials (SPIRIT) figure of the Older Persons ENablement And Rehabilitation for Complex Health conditions (OPEN ARCH) intervention

### Study setting

The study will be conducted at two sites in Far North Queensland (Australia): Cairns and Kuranda. Cairns is a regional centre on the north-east coast of Australia with a population of 160,285, of whom 11.6% are over the age of 65 years [13]. Kuranda is a rural community adjacent to Cairns in the north-west with a population of 4684, of whom 16.4% are over the age of 65 years [14].

### Trial design

A multicentre, randomised controlled trial using a stepped wedge cluster design with repeated cross-sectional samples will be utilised to measure participants’ acceptability of the model, health outcomes, services utilisation and economic viability of the OPEN ARCH intervention (see Fig. 2).

**Fig. 2 Fig2:**
[figure not shown]
Schematic of the study design. Adapted from Hemming et al. [38]

The stepped wedge design allows all participants to receive the intervention, which is the preferred methodology for studies where the intervention is predicted to do more good than harm [15]. It allows patients to act as their own controls and detect trends and changes associated with time [15, 16].

### Recruitment of general practitioners

The OPEN ARCH intervention builds on a successful collaboration between Cairns and Hinterland and Hospital and Health Service clinicians with local GP practices. Individual GPs with an interest in geriatrics will be approached via clinical and professional networks to participate in the study. A minimum of 10 GPs within the Cairns area (urban) and the Cairns Hinterland region (rural) will be approached to participate in the study. The project manager will conduct informed consent for the GP to participate.

### Randomisation of general practitioners

All recruited GPs will be randomised as ‘clusters’ at baseline using simple randomisation [17]. Such cluster randomisation allows control for the ‘between GPs variance’. A minimum of two clusters (two GPs) will be commencing the intervention at each step, as per the recommendations of Barker et al. [16], to ensure that the intervention effect estimator maintains the nominal 5% significance level and is reasonably unbiased. All clusters will ultimately receive the intervention for the same length of time.

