### Statistical methods to assess intervention effect

The primary outcome measures, including Emergency Department (ED) presentations, hospital admissions, in-patient bed days, allied health and support services utilisation, will be analysed as panels between each cross-sectional time point of the stepped wedge design, comparing primary outcomes within and between clusters. Each cross-section will include participants undertaking the intervention as well as those receiving standard care (pre-intervention component). In addition to assessing intervention effects, the stepped wedge design can also model the effects of time to determine whether the time of intervention (intervening early versus intervening late) impacts the effectiveness of the intervention. Secondary outcome measures, including functional status, ISAR and QoL measures, will be compared for the pre versus post intervention periods, for each participant, and thus the participants will act as their own control. Participants’ experience of the OPEN ARCH intervention as measured by the Likert scale responses will be analysed using descriptive statistics.

Within-cluster and between-cluster variance, treatment outcomes for intervention versus pre-intervention, across time, will be examined by applying a generalised linear mixed model (GLMM), as recommended for small cluster designed stepped wedge studies [16]. GLMM models can be adjusted for unequal numbers within clusters and cope with non-parametric data distributions. Within the GLMM, primary and secondary outcomes will be assessed against time and intervention status, represented as fixed effects, while study clusters and clients will be represented in the model as random effects [16]. Secondary outcome analyses will include *t* tests (for continuous data), chi-square tests (for proportions) and GLMMs where applicable, to control for demographic differences. All statistical tests will be two-sided and performed using a 5% significance level with no adjustment for multiplicity. Data analysis will be performed using STATA version 15 [18].

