#### Frequency of analyses

All data will be collected at baseline ‘0’ with retrospective collection for 3 months to time point ‘– 1’, following every 3 months of data collection, at time points ‘1’, ‘2’ and ‘3’ (see Fig. 2), except for participants’ experiences, which will be collected at the end of the study period.

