### Limitations

The study populations are, by definition, at risk of natural functional and cognitive decline that may be marked over the study period. Although the study design applies multiple methods to best capture intervention effects, the benefits in slowing down deterioration may not be successful in some participants due to their frailty. Within the quantitative methods are cross-sectional and case–control (pre–post intervention) analysis, which will assess between and within clusters differences. The pre–post analyses will utilise paired analyses where each participant acts as their own control. These methods plus the inclusion of qualitative surveys should tease out even minor benefits of OPEN ARCH, when presented with accelerated decline. The sample size calculation has allowed attrition, so these factors should allow statistical significant effect size within OPEN ARCH achievable.

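### The trial is labelled and sized as repeated cross-sections but follows a closed cohort, and its statements on exposure length and concurrent comparison do not all fit one schedule

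*Protocol article*

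**What the plan says.** **Design label.** The abstract says that the trial "uses a stepped wedge cluster design with repeated cross-sectional samples". The Trial design section repeats this, and the Sample size section follows published guidance for that design.

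**Who is measured.** Each GP recruits 10–12 participants (at least 10 GPs, 120 people). "Data will be collected on each participant at 3-month intervals", at −3, 0, 3, 6 and 9 months. Trial design says of the stepped wedge that "It allows patients to act as their own controls and detect trends and changes associated with time". Limitations says that the pre–post analyses "will utilise paired analyses where each participant acts as their own control". Statistical methods puts cluster and client in the model as random effects. No fresh sample per period is described.

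**Timing.** Randomisation of general practitioners states: "All clusters will ultimately receive the intervention for the same length of time". It also asks for at least two GPs per step. Frequency of analyses describes a baseline "with retrospective collection for 3 months to time point" −1, then points 1, 2 and 3 at three-monthly spacing. Statistical methods states: "Each cross-section will include participants undertaking the intervention as well as those receiving standard care (pre-intervention component". It makes time a fixed effect without saying which clock is meant. The text gives no number or spacing of steps; Fig. 2, which may show them, is not available here.

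**The concern.** Two things do not line up. First, a sample size framed for a new sample in each period is paired with an analysis model for the same people measured repeatedly, so the two sections describe different trials. Second, the sentences on equal exposure, on the −3 to 9 month schedule and on both conditions being present in every cross-section are hard to satisfy together.

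The randomised information in a stepped wedge comes from comparing, within a calendar period, clusters that have crossed over with clusters that have not. Where a period holds only one condition, the estimate leans on before–after change. That is a weak basis in a frail group, for whom Limitations itself expects decline over the study. The choice of clock also decides whether the time effect can be separated from the intervention at all.

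**Working it through.** **Reproducing the plan's figure.** The attrition step checks: 90/(1 − 0.25) = 120, that is 9 retained per GP in 10 GPs. The 80% power cannot be reproduced, because the article gives no baseline level, no standard deviation and no number of steps.

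**Direction of the sample-size mismatch.** In one case (three steps, four windows, 9 per GP, ICC 0.10, assumed baseline proportion 0.3, 9-point absolute drop), treating the data as cross-sections gives power 0.21. Treating them as a cohort, with half the within-cluster variance assumed to lie between persons, gives 0.35. The cohort model therefore gains power; the issue is that the stated calculation is not for this design.

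**Layouts that the text allows.** Five time points give four 3-month windows.

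- *One study calendar, sustained delivery.* Windows are −3–0, 0–3, 3–6 and 6–9. With three steps at 0, 3 and 6 months, observed exposure is 9, 6 and 3 months. Only 0–3 and 3–6 contain both conditions: 2 of 4.
- *Each GP's own clock, one control quarter then three intervention quarters.* Exposure is 9 months for all. With S steps three months apart there are S + 3 calendar quarters, of which S − 1 contain both conditions: 4 of 8, 3 of 7, 2 of 6 and 1 of 5 for S = 5, 4, 3 and 2.
- *One study calendar, a fixed 3-month intervention, later windows left out.* Exposure is equal; 2 of 4 windows contain both conditions.

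In each layout the first window is all control and the last all intervention.

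**Aliasing on the own clock.** The quarter ending at label 0 is always control; those ending at 1, 2 and 3 are always intervention. The intervention indicator is then the sum of the indicators for labels 1, 2 and 3. The design matrix with four label effects plus intervention has rank 4 for 5 parameters, so the effect is not estimable. With calendar quarter as time, it is.

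**Value of a wider records extract.** Assumptions: five three-monthly steps of 2 GPs, own clock, 9 per GP, ICC 0.10, total variance 1, within-person correlation r = 0, 0.3 or 0.5. For cluster-period means, V = 0.10·J + (0.90/9)·[r·J + (1 − r)·I], with calendar-quarter fixed effects and generalised least squares. Minimum detectable effect (MDE) = 2.80 × SE, in SD units.

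- Own four quarters only: SE 0.1652 / 0.1458 / 0.1277; MDE 0.46 / 0.41 / 0.36.
- All earlier quarters added, post-start data stopped at 9 months: SE 0.1455 / 0.1256 / 0.1079; MDE 0.41 / 0.35 / 0.30. Variance reduction, for example 1 − (0.1455/0.1652)² = 22%; then 26% and 29%.
- All eight quarters, every quarter after crossover counted as intervention: SE 0.1316 / 0.1112 / 0.0945; MDE 0.37 / 0.31 / 0.26. Variance reduction 1 − (0.1316/0.1652)² = 37%; then 42% and 45%.

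The number of mixed quarters stays at 4 of 8 in all three. What changes is the number of GPs within them: in quarter 2, own-quarter data give 2 control and 2 intervention GPs; the wider extract gives 8 and 2.

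**The case against.** A reader might infer that equal exposure is impossible under this schedule. The documents do not support that. On each GP's own clock exposure is equal, and the word ultimately may cover delivery that continues after the last data point. The equal-exposure sentence is in tension with one reading, not shown to be false. That said, the Trial status section places the study 6 months after baseline, which suggests a single study clock, the reading under which the tension arises.

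The counts rest on assumed steps. The 9/6/3 pattern needs three steps and 4 of 8 needs five; neither is in the text, and Fig. 2 may settle both. The two clocks are not strict alternatives either, since the common calendar also leaves half of its windows without a concurrent comparison. An all-control first period and an all-intervention last period are normal in a stepped wedge. What is wrong is only the sentence saying that every cross-section contains both.

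A reader might also infer that the label invalidates the analysis, or that the planned model cannot be fitted. Neither follows. The client random effect already makes it a cohort model. The aliasing arises only if the −1 to 3 label is used as time on an own-start clock; on a common calendar the label is a calendar period. Coding of time may also be left to an analysis plan not shown.

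Finally, the wider extract creates no additional mixed quarters, and its larger gain counts up to 21 months of post-start time for the first GPs against 9 for the last, which departs from equal exposure. These objections narrow the point. They leave the label and sample-size mismatch, and the incorrect concurrency sentence, in place.

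**Conclusion.** The point holds in limited form. The cross-sectional label and sample-size basis contradict the closed cohort that the article describes; this needs no figure and no assumption. The concurrency sentence is untrue for at least the first and last windows in every layout tried. The equal-exposure sentence needs a stated clock before it can be squared with the schedule.

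The article neither proves unequal exposure nor invalidates its own model. The practical size is the precision left unused if hospital records are restricted to each participant's own four quarters: about 22–29% of the variance with post-start data capped at 9 months, or 37–45% without the cap. Both ranges are conditional on the assumed five steps of 2 GPs, own clock, 9 per GP, ICC 0.10 and within-person correlation of 0 to 0.5.

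**What to change.** 1. Describe the trial as a closed-cohort stepped wedge and restate the sample-size basis for a cohort, including the within-person correlation assumed.
2. State in the text the number and spacing of steps and the clock on which −3 to 9 months runs. Reconcile the equal-exposure and concurrency sentences with it.
3. Fit calendar period, not the −1 to 3 label, as the time effect.
4. For ED presentations, admissions and bed days, extract the routine hospital records for every participant over the common calendar window. State in advance whether quarters beyond 9 months after a GP's start count as intervention.

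Items 1 to 3 cost wording and a model specification. Item 4 widens the date range of an extract already planned from Queensland Health records, with no added participant burden, but may need a consent or ethics note. It has two statistical costs. Using later quarters makes exposure longer and unequal between GPs. Control time before recruitment is conditional on having survived and lived in the community until recruitment, which could bias the comparison and should be examined in a sensitivity analysis.
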